##### Aim 2: Personal Network Study

We will use quantitative personal network analysis to address Aims 2a, b, and c. Personal network measures consist of compositional variables, which describe who is in the network, and structural variables, which measure how network alters are arranged around the ego. Personal network measures will be obtained at two points, baseline and 12-month follow-up. Compositional variables for each alter include: demographic data (ie, sex and age); relationship to participant (ie, relationship, how close, frequency of interaction, and smoking- and quitting-related support); and smoking-related information (ie, use of tobacco products, previous and current smoking status, and quit attempts). Structural variables will be calculated in R package *egor* based on alter pairs that very likely interact and include: density (ie, the extent to which all possible connections between alters are present), alter centrality measures (ie, to identify the most central individuals in the network), network centralization (ie, the extent to which a network is dominated by one or a few alters), and measures of subgroups (ie, to identify cohesive or disconnected subgroups). Additionally, some combined compositional and structural variables will be calculated with smoking status and alter centrality measures.

Descriptive statistics will be run on all compositional and structural personal network variables at both time points. We will assess using analysis of variance differences in network measures between the Helpers Stay Quit (vs usual care completers, completers who carried out helping conversations (vs no helping conversations), and completers who relapsed (vs abstained). Paired samples *t* tests will be used to compare network measures between the two different points.

Qualitative analysis will be used to address Aims 2a, b, and c, along with the quantitative personal network analysis. Participants were shown a series of network visualizations to facilitate discussion during the interview. Interviews are transcribed, using a verbatim transcription protocol, and analyzed using a combination of a priori (theory-based) coding combined with emergent codes to produce themes, which are used to assign higher-level meaning to the data [77-79]. Manual coding using ATLAS.ti (Scientific Software Development GmbH) will be compared to AI coding using natural language processing in R. Both descriptive and interpretive codes will be used in this analysis, with development of additional codes for emergent themes and issues [79].

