Participants in the longitudinal embedded personal network study (egos) completed a personal network telephone interview in which they named members of their personal network with whom they had at least monthly contact (alters). With each monthly text message survey, egos who reported offering a helping conversation were given a link to an online survey that could be passed to an alter who could respond anonymously. The alter survey queried smoking status, content of the helping conversation, and the alter’s reaction to the helping conversation. Results showed that a participant’s behavior to help others quit extended to their personal networks, where 89% of abstainers offered helping conversations, and 86% abstained from smoking for the 6-month study duration (n=64) [38]. Abstaining individuals significantly increased the number of nonfamily members (mean difference [MD] 1.41; *P*<.001) and smokers in their networks (MD 0.77; *P*=.006) at follow-up. This change provided participants with more opportunities to carry out helping conversations. After receiving a helping conversation, alters reported positive changes in cessation-related behavior. These findings further support the potential of personal network behavioral interventions, like Helpers Stay Quit, to facilitate smoking relapse prevention.

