## Methods

### Study Design

This is a 2-group, parallel pRCT with embedded personal network study comparing: (1) Intervention: Helpers Stay Quit training, and (2) control: quitline postabstinence follow-up usual care. The primary outcome is smoking status at 6 and 12 months. The purpose of the pRCT is to assess if a novel behavioral intervention (Helpers Stay Quit) overall has any effect on relapse in newly abstinent smokers following standard quitline treatment compared to quitline usual care, in real-world conditions of serving state quitline client populations. Relapse and the number of helping conversations will be assessed using a text survey weekly for the first 6 months and biweekly for months 7‐12. The prestudy quitline treatment, quitline referral, study recruitment, screening, consent, and prerandomization and run-in period are depicted in Figure 1. The postrandomization study intervention exposure, assessment intervals, and qualitative interviews are depicted in Figure 2.

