Participants completing every protocol activity and qualifying for every incentive could receive a total of US $419. A breakdown of the study protocol items and their compensation rates is as follows: baseline (US $20), social network assessment 1 (US $25), training (US $40), incentive for completing training within two weeks (US $10), 3-month survey (US $20), 6-month survey (US $20), 9-month survey (US $20), 12-month survey (US $20), bonus for completing all 4 surveys (US $5), social network assessment 2 (US $25), qualitative personal network interview (US $30), weekly text survey (24 total; US $4 each), biweekly text survey (12 total; US $4 each), 6-month follow-up specimen completion incentive (US $15), 12-month follow-up specimen completion incentive (US $15), and maximum completion bonus for completing all study activities (US $10).

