### Sample Size, Power Estimates, and Analysis

#### Power and Sample Size for Pragmatic Randomized Controlled Trial (pRCT)

A sample size of 940 participants would yield 80% power to detect a difference in smoking cessation rates between arms of 10%, assuming a conservative control arm rate of 0.25 [65], 30% dropout, and a noncontinuity corrected *χ*^2^ test. This difference is smaller than that found in the preceding pilot feasibility study (difference=46%); this effect size was chosen as a clinically significant difference with public health implications and is feasible, given the pilot results. This sample size also yields 90% power to detect standardized effect sizes for continuous secondary outcomes of Cohen *d*=0.26, a small-to-medium effect size, and considered to be a good estimate for a minimum important difference for patient-reported outcomes.

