##### Aim 1: Abstinence and Relapse

Abstinence rates at 6- and 12-months postrandomization and biochemically confirmed abstinence at 6- and 12-months postrandomization will be compared between arms using multivariable logistic regression for each outcome (6- or 12-months). Independent variables will include intervention status, strata (race and ethnicity), quitline, and covariates (as described above). We will compare time to first relapse using Cox models and Kaplan-Meier curves. The number of relapses and helping conversations will be compared between study arms using Poisson regression, with the zero-inflated Poisson or negative binomial model used if appropriate. We will carry out secondary analyses using general linear mixed models to examine change in cognitive and emotional measures of participant-reported outcomes (described above in the General Quantitative Approaches section) for participants randomized to receive Helpers Stay Quit compared to participants randomized to the usual care arm.

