##### Aim 3: Mediational Analysis

Using data from Aims 1 and 2, we will use multiple mediation models to investigate mechanisms of Helpers Stay Quit. Specifically, we will estimate the direct effects of the intervention on abstinence, as well as the indirect effects that are mediated through the personal networks of participants and longitudinal change in scores collected through surveys. Potential candidates for mediation include the number of helping conversations, change in personal network variables (smoking status, smoking status and degree centrality, smoking status and sex, density, and degree centralization), and change in patient-reported outcome variables from the cognitive and emotional measures. To narrow down the list of potential mediators from the conceptual framework, we will first examine relationships between the intervention arm and the mediator, as well as the mediator and the outcome variable. Variables associated with both the intervention and abstinence, with a *P* value of .1, will be included in this analysis as potential mediators. Variables associated with abstinence but not treatment arm at the 0.1 alpha level will be included as a covariate but not explored further as a mediator. For those who meet the initial criteria for a mediator (associated with both intervention arm and outcome), we will examine direct and indirect effects using causal mediation modeling [80].

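### Aim 2 relates helping conversations to network measures only as any versus none, with no stated adjustment for arm, although the number of conversations is collected throughout the year

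*Protocol article*

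**What the plan says.** The Study Design section collects conversations repeatedly and as a number: "Relapse and the number of helping conversations will be assessed using a text survey weekly for the first 6 months", then every two weeks up to month 12. The payment schedule under Ethical Considerations gives the occasions: "weekly text survey (24 total; US $4 each), biweekly text survey (12 total; US $4 each", so 24 + 12 = 36 per participant.

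Two of the three aims keep the number. Aim 1: "The number of relapses and helping conversations will be compared between study arms using Poisson regression", with zero-inflated or negative binomial alternatives. Aim 3: "Potential candidates for mediation include the number of helping conversations, change in personal network variables".

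Aim 2 does not. Its analysis of variance compares the two arms and then "completers who carried out helping conversations (vs no helping conversations), and completers who relapsed (vs abstained". The section gives no reason for cutting at zero, does not confine the contrast to one arm and names no covariate.

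The only figure on how common conversations are comes from the single-group pilot of trained participants over 6 months: "89% of abstainers offered helping conversations".

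**The concern.** The Discussion describes the intervention as changing the network by way of helping conversations. The link between conversations and network measures is therefore of real interest, and the any/none contrast is the only stated quantitative analysis of it. Aim 1 compares the count between arms. Aim 3 screens conversations and network change as parallel candidates against arm and abstinence, not against each other.

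Three things follow from the stated form.

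- A participant with one conversation is grouped with a participant with thirty, so a graded relation is measured coarsely.
- If most trained participants have at least one conversation, the comparison group is small in that arm.
- The intervention is built to produce conversations, so a contrast pooled over arms and not adjusted for arm partly compares the arms. A network difference due to the training by any route could then be credited to helping behaviour.

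**Working it through.** **1. The plan's own sample size.** Inputs from the power section: 25% versus 35%, 80% power, uncorrected chi-square, 30% dropout. Two-sided alpha of 0.05 is assumed.

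n per arm = [1.96·√(2·0.30·0.70) + 0.8416·√(0.25·0.75 + 0.35·0.65)]² / 0.10² = (1.270 + 0.542)² / 0.01 ≈ 329. Then 329/0.70 = 470 per arm, 940 in total. The stated figure reproduces, and 329 per arm (658 in all) is used below as the number of completers.

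**2. Size of the group with none.**
- Intervention arm at the pilot's rate: 329 × 0.11 ≈ 36, against 293 with any. The difference detectable with 80% power is d = 2.80·√(1/36 + 1/293) ≈ 0.49, against 0.31 for an even split of 329.
- Both arms pooled: the control rate is not given, so 30-89% is assumed. None = 36 + 329 × 0.70 ≈ 266 at 30%, and 36 + 36 ≈ 72 at 89%.

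**3. Information kept by the cut, if the relation is graded.** For a normally distributed dose split so that a proportion p has any, the share kept is φ(z_p)² / [p(1−p)]. Power is about Φ(2.80·√share − 1.96), starting from 80% for the undivided dose.

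| Setting | p | Share kept | Power on any/none |
|---|---|---|---|
| Intervention arm, or pooled with controls at 89% | 0.89 | 0.36 | 39% |
| Pooled, controls at 70% | 0.795 | 0.495 | 50% |
| Pooled, controls at 50% | 0.695 | 0.58 | 57% |
| Pooled, controls at 30% | 0.595 | 0.62 | 60% |

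**4. The same question with counts.** Simulation settings: 329 per arm, negative binomial counts with dispersion 0.5 to 2 (assumed), 89% with any in the intervention arm and 30%, 60% or 89% in control, arm-adjusted linear model, 2,000 replicates per setting.
- Effect linear in log(1 + count): 78-82% power on the count, 35-53% on any/none.
- Effect a pure threshold at the first conversation: 33-52% on the count, 79-81% on any/none.

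**5. What the pooled contrast picks up if arm is ignored.** Assume no effect of helping and an arm effect of d = 0.26 on the network measure. That value is borrowed from the detectable effect for continuous secondary outcomes; it is not an estimate for networks. With a control rate q, the expected any/none difference is 0.26 × [0.89/(0.89+q) − 0.11/(1.11−q)].

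| q | Any / none | Expected difference | SE | z | Rejects |
|---|---|---|---|---|---|
| 0.30 | 392 / 266 | 0.26 × 0.612 = 0.159 | 0.079 | 2.00 | 52% |
| 0.60 | 490 / 168 | 0.26 × 0.382 = 0.099 | 0.089 | 1.11 | 20% |
| 0.75 | 540 / 118 | 0.26 × 0.237 = 0.062 | 0.101 | 0.61 | 9% |

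The nominal rate is 5%.

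**6. Dependence on texts answered.** With an assumed 5% chance of a reported conversation per text, the chance of being labelled as any is 1 − 0.95³⁶ = 84% after 36 answered texts and 1 − 0.95¹² = 46% after 12.

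**The case against.** - **Thin, not near-empty.** A reader might infer a near-empty comparison cell. The document does not support this. Its only rate leaves about 36 intervention completers with none, and the contrast is not said to be confined to that arm. The group could shrink over 12 months with 36 prompts, but no figure is given.
- **The power loss is conditional.** A reader might infer that the cut simply discards half of the power. That depends on a graded relation, an assumed dispersion and an unstated control rate, and it reverses under a threshold. Nothing in the document favours either shape.
- **Arm and response are not problems of the cut alone.** An unadjusted count would also carry the arm effect and also rise with texts answered. This stands: adjustment is needed whichever form is used.
- **A joint model is not excluded.** The sentence lists three groupings under one analysis of variance. If they enter one model together, arm is adjusted for and step 5 falls away. The text reads more naturally as three comparisons but does not settle it.
- **The randomised comparison tests Aim 2 itself.** Aim 2 asks for the effect of the intervention on networks, and the arm contrast in the same sentence addresses that. The any/none contrast should not be read as the trial's only test of mechanism.
- **A count regression has its own weakness.** The pilot section reports that networks with more smokers and nonfamily members gave more opportunities for conversations, so the direction may run from network to conversations. This stands and shapes the fix.
- **A condensed article leaves detail elsewhere.** This is true of definitions and text non-response. The method and the grouping, however, are stated, and the Conclusions say that trial papers will follow the analytic plans given here.

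**Conclusion.** The point holds in a limited form. Aim 2 fixes an any/none grouping for a variable collected as a number and used as a number elsewhere. No stated analysis relates that number to network measures, and no arm adjustment is stated for this contrast.

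If the relation is graded in log count, a test with 80% power on the count has roughly 35-60% on any/none. If the relation is a threshold at the first conversation, any/none is the stronger test. If the contrasts are run separately and arm matters for networks, the pooled contrast can reject well above 5% with no helping effect: 52%, 20% or 9% under the assumptions above.

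These sizes rest on 30% dropout, the pilot's 89% carrying over to the trial, and assumed control rates, dispersion and arm effect. The contrast is exploratory and non-randomised, and the primary outcome, sample size and between-arm inference are untouched. It is a cheap improvement to a stated method.

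**What to change.** In the Aim 2: Personal Network Study section:

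1. Regress each 12-month network measure on log(1 + number of helping conversations), adjusting for arm, the baseline value of the same measure and the number of text surveys answered.
2. Keep the any/none contrast, with the same adjustments, as a supplement.
3. Report both as non-randomised associations, because larger or more smoker-rich networks also give more opportunity for conversations.

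The cost is analysis-plan wording only, since every variable is already collected. The downside is lower power for the count analysis under a pure threshold (about 33-52% where any/none has about 80%), which is why the any/none contrast stays.

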##### Aim 3: Mediational Analysis

Using data from Aims 1 and 2, we will use multiple mediation models to investigate mechanisms of Helpers Stay Quit. Specifically, we will estimate the direct effects of the intervention on abstinence, as well as the indirect effects that are mediated through the personal networks of participants and longitudinal change in scores collected through surveys. Potential candidates for mediation include the number of helping conversations, change in personal network variables (smoking status, smoking status and degree centrality, smoking status and sex, density, and degree centralization), and change in patient-reported outcome variables from the cognitive and emotional measures. To narrow down the list of potential mediators from the conceptual framework, we will first examine relationships between the intervention arm and the mediator, as well as the mediator and the outcome variable. Variables associated with both the intervention and abstinence, with a *P* value of .1, will be included in this analysis as potential mediators. Variables associated with abstinence but not treatment arm at the 0.1 alpha level will be included as a covariate but not explored further as a mediator. For those who meet the initial criteria for a mediator (associated with both intervention arm and outcome), we will examine direct and indirect effects using causal mediation modeling [80].

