### Research Objectives

This study is designed to assess the effect of Helpers Stay Quit training on the proportion and duration of participants maintaining abstinence or relapsing over time and on participants’ personal network structure and interactions related to smoking and smoking cessation. Primary and secondary research questions are as described in study-specific aims (Textbox 1).

Textbox 1.The Helpers Stay Quit study-specific aims.Aim 1: Using a 2-group, pragmatic randomized, controlled trial (pRCT; N=940) in which abstinent smokers (2-6 weeks abstinent) are randomized to the Helpers Stay Quit intervention or quitline follow-up usual care, to evaluate the effectiveness of Helpers Stay Quit on:Smoking status (30-day and 7-day point prevalence abstinence) at 6- and 12-month intervals (primary outcome).The number, timing, and duration of participants’ lapses and relapses to smoking (secondary outcome).Rates of participants’ self-reported delivery of helping conversations to other tobacco users (secondary outcome).Aim 2: embed a mixed methods social network study into the pRCT to examine the Helpers Stay Quit effects on:Composition and structure of participants’ personal networks.Characteristics of participants’ personal networks over the course of the study (eg, proportion of smokers in personal network).Spread of smoking cessation-related information, assistance, and behaviors from participants to others in their personal networks.Recipients of helping conversations report about smoking-related interactions and information exchange with participants and associated cessation-related behavior change.Aim 3: using personal network metrics derived from the personal network study (eg, size, composition, and structure), conduct mediational analyses of personal network effects on the primary and secondary study outcomes in Aim 1.

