### Measures and Data Collection for Embedded Mixed Methods Personal Network Study

#### Overview

Personal network recruitment, screening, and inclusion and exclusion criteria are the same as for the main study. All main study participants (egos) complete two online personal network assessments, one at baseline and the other at 12 months post baseline. Personal network assessment questions address network composition and structure and are administered using REDCap (Research Electronic Data Capture; Vanderbilt University) [51-54]. Each participant (ego) is asked to name 25 individuals (alters) with whom they have had any kind of contact over the past six months [55,56]. Egos are then asked questions about each alter to capture the compositional variables, such as the proportion of individuals who smoke in their personal network and the social support and influence for abstinence. Personal network structure is defined by asking the participant (ego) whether each unique pair of alters talks to each other independently of ego [52].

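### Personal-network change is observed only at 12 months, after or alongside the outcomes it is meant to mediate, so Aim 3 cannot tell network effects on abstinence from abstinence effects on networks

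*Protocol article*

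**What the plan says.** **Network measurement.** Under Aim 2: Personal Network Study, "Personal network measures will be obtained at two points, baseline and 12-month follow-up". The Overview of the embedded network study agrees: participants "complete two online personal network assessments, one at baseline and the other at 12 months post baseline". Table 1 shows no other network assessment.

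**Outcomes.** Under Study Design, "The primary outcome is smoking status at 6 and 12 months". The number, timing and duration of lapses and relapses are secondary outcomes, tracked by text survey weekly for six months and every two weeks after that. Time to first relapse is analysed with Cox models.

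**Mediation.** Textbox 1 sets Aim 3 as using network metrics to "conduct mediational analyses of personal network effects on the primary and secondary study outcomes in Aim 1". The Aim 3 analysis section then plans direct effects on abstinence and "indirect effects that are mediated through the personal networks of participants and longitudinal change in scores collected through surveys". The candidates are the number of helping conversations, change in network variables, and change in the cognitive and emotional scores. A candidate is kept if it is associated with both arm and abstinence at P = .1, and is then analysed by causal mediation modelling. For the others, "Variables associated with abstinence but not treatment arm at the 0.1 alpha level will be included as a covariate".

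**The concern.** A mediator must come before the outcome it explains. Here the only post-baseline network measurement comes after one primary time point and coincides with the other. If relapse or continued abstinence changes who is in the network, or how central its smokers are, that change will be associated with the outcome and, whenever the intervention works, with arm as well. It can then pass both screens and be reported as part of the reason why participants stayed quit. Selecting by association with abstinence does not guard against this, because it favours variables that abstinence alters.

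The covariate rule has the same weakness. A 12-month network variable that responds to abstinence but misses the arm screen enters the model as a covariate, so the direct effect is conditioned on a possible consequence of the outcome.

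At stake is the interpretation of the network mechanism, one of the trial's three specific aims. The comparison of abstinence between arms is not at stake.

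**Working it through.** **Step 1: order in time.** Second network assessment: month 12.

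| Aim 1 outcome | When determined | Network change observed |
|---|---|---|
| 6-month abstinence | month 6 | 6 months after the outcome |
| Time to first relapse, number of relapses | months 0 to 12 | after most events |
| 12-month abstinence | month 12 | at the same time |

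The network questions ask about a stated period: each participant "is asked to name 25 individuals (alters) with whom they have had any kind of contact over the past six months". At month 12 this covers roughly months 6 to 12, which lies wholly after 6-month abstinence has been settled.

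**Step 2: do the documents allow for the reverse direction?** Yes. The section on the conceptual basis of the intervention speaks of feedback loops around relapse. The Discussion (Principal Findings) describes smoking identity and smoking behaviour as affecting each other, and cites studies of network change after cessation. Aim 2 itself compares network measures between completers who relapsed and those who abstained.

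**Step 3: the plan's own sample size.** Inputs from the power section: control rate 0.25, difference 0.10, power 80%, uncorrected chi-square test, 30% dropout. A two-sided alpha of 0.05 is assumed, as it is not stated.

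n per arm = [1.96 × √(2 × 0.30 × 0.70) + 0.8416 × √(0.25 × 0.75 + 0.35 × 0.65)]² / 0.10² = (1.2702 + 0.5422)² / 0.01 = 328.5, rounded up to 329.

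With dropout: 329 / 0.70 = 470 per arm, 940 in total. The stated figure reproduces, so 329 analysed per arm is used below.

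**Step 4: apparent mediation when none exists.** Let Y be abstinence (0.25 against 0.35) and let M = −g × Y + N(0,1) be network change, so M is caused only by Y. The shift g, in SD units, is assumed; the documents give no value. With linear product-of-coefficients mediation:

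- Within-arm variance of Y: v = (0.1875 + 0.2275) / 2 = 0.2075
- Arm to mediator: a = −0.10g
- Mediator to outcome, given arm: b = −gv / (1 + g²v)
- Apparent mediated share: ab / 0.10 = g²v / (1 + g²v)

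Example, g = 0.5: 0.25 × 0.2075 = 0.0519, and 0.0519 / 1.0519 = 4.9%.

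Results, with 3,000 simulated trials per row:

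| g (SD) | Share, formula | Share, simulated | Passes both P<.1 screens | Both paths P<.05 |
|---|---|---|---|---|
| 0 | 0% | 0.01% | 1% | 0.2% |
| 0.2 | 0.82% | 0.77% | 9% | 3% |
| 0.3 | 1.83% | 1.85% | 12% | 7% |
| 0.5 | 4.93% | 4.98% | 17% | 10% |
| 0.8 | 11.72% | 11.49% | 25% | 16% |
| 1.0 | 17.18% | 17.45% | 33% | 22% |

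The true mediated share is zero in every row. The screening rates are for one candidate variable; the plan lists several.

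**Step 5: the covariate rule.** In the same linear model, conditioning on M changes a 0.10 effect to 0.10 / (1 + g²v): 0.095 at g = 0.5 and 0.083 at g = 1.0. These are averages over all trials. In a trial where M misses the arm screen, the observed arm difference in M is small, so the shift under this rule is smaller than the average. The direction of the fault is clear; its size is probably modest.

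**The case against.** **Aim 3 is mechanistic.** The effectiveness analysis does not use it, the objective says only that outcomes may be mediated, and the limitations disclaim identifying which component works. This stands, and it limits the severity. It does not answer the timing problem, because the plan still names causal mediation modelling and the limitations do not mention timing.

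**The bias may be small.** This also stands. A reader might infer that the indirect effects will certainly absorb reverse causation, or that a false network mechanism will be reported. The documents do not support that: the network response is unknown, a 0.2-0.3 SD shift gives only 1-2%, and even at 1.0 SD about two thirds of simulated trials do not pass a given variable through both screens. The simulation is also linear and without covariates, so it illustrates the fault and does not reproduce the planned model.

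**Other mediators.** A reader might extend the point to the survey scores and helping conversations. Scores are collected at 3, 6, 9 and 12 months and helping conversations by frequent text survey, so both can be cut off before the outcome. The choice of lag is ordinary analysis-plan detail.

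**Outcomes covered.** The Aim 3 analysis section speaks only of abstinence; the wider scope comes from Textbox 1. That is fair, but the section does not exclude the 6-month time point, and the two passages should agree.

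**Reference period.** For 12-month abstinence, contacts over the previous six months fall mostly before the 7- or 30-day outcome window. This softens the word concurrent, but relapse earlier in that period or before it can still have shaped the network.

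**Network size.** Textbox 1 names size as an example metric, and a reader might infer that it is fixed at 25. Participants are asked to name 25; the article does not say that fewer is impossible, and size is absent from the Aim 3 mediator list. This is not part of the finding.

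**Conclusion.** The point holds for the network mediators. With assessments only at baseline and month 12, network change cannot act as a prior cause of 6-month abstinence or of relapses dated before month 12, and its relation to 12-month abstinence has no established direction. This follows from the schedule and needs no assumption; an unseen analysis plan cannot add an earlier network wave, since the schedule is fixed and enrolment is complete.

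The amount of bias does rest on an assumption, namely how far relapse or abstinence moves the network measure, so the tabulated shares show a range and are not a prediction for this trial. The covariate rule is a second, smaller fault of the same kind. The plan should be corrected before the mediation analysis is run.

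**What to change.** 1. Do not use 12-month network change as a mediator of 6-month abstinence, time to first relapse or number of relapses. Bring Textbox 1 and the Aim 3 section into line on this.
2. Report the relation of network change to 12-month abstinence as an exploratory concurrent association, and add the timing to the stated limitations.
3. Keep causal mediation claims for mediators measured before the outcome: for example, score changes to month 3 or 6 and helping conversations in months 1-6, with 12-month abstinence as the outcome.
4. Smoking before the mediator time is itself affected by treatment and confounds the mediator-outcome relation. Handle it with a method built for that case (for example, interventional indirect effects or weighting), not by entering it as a simple covariate.
5. Replace the covariate rule with adjustment for baseline covariates, and do not adjust for unselected post-randomisation candidates.

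Cost: wording and some added analysis for item 4; no new data. The real loss is the causal claim through 12-month network change, which the measurement schedule cannot support.
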